## **“Young fit and happy”**

### **“Meaningful physical activity as means to improve quality of life and prevent weight gain in over-weight and obese adolescents.”**

The overall purpose of this study is to establish an effective intervention aimed at enhancing meaningful physical activity and quality of life in overweight and obese adolescents by establishing an activity plan and give individualised web-based counselling. Further, the purpose is to better understand how overweight and obese adolescents experience being exposed to a web-based intervention program. To participate in an intervention puts demands on the adolescents to change their lifestyle in order to reach their goals. The need for more comprehensive knowledge about what works according to weight and fitness, what motivates the adolescents to change and finally how adolescents experience interventions that require lifestyle changes is needed.

Until now, no single intervention has proved to be effective in treating and/or preventing overweight and obesity in adolescents. However, a systematic review on treatment of obesity shows that combined behavioral lifestyle interventions compared to standard care or self-help can produce a significant and clinically meaningful reduction in overweight children and adolescents (Oude Luttikhuis 2009). Another systematic review focusing on prevention strategies showed that combining dietary and physical activity approaches did not significantly improve BMI, but some studies that focused on dietary or physical activity approaches showed a small but positive impact on BMI status. Nearly all studies included in the review resulted in some improvement in diet or physical activity. (Summerbell et al 2009). Even though many of the programs have little impact on BMI, the increase in physical activity and improved diet is shown to have a positive impact on the adolescents' health, which is a desirable outcome in itself (Blair et al 1999). In “Young, fit and happy” it is our assumption that increased physical activity improves the adolescents' fitness (health) and their quality of life. The challenge is to get the adolescents' motivated for lifestyle changes in order to make them permanent. Focusing on how the adolescents are doing through the process and how they experience being in the process of an intervention should give us valuable knowledge on how to design effective theory-based programs for treating and preventing overweight and obesity. Therefore the purpose of this study is twofold, to test a web-based intervention by a randomized controlled trial and to gain in depth knowledge on the adolescents' experiences of being overweight and being exposed to a web-based intervention program. In a review, web-based weight management programs for overweight children and adolescents show a big potential for weight management. However, more research is needed to investigate types of web-interventions appropriate for boys and girls in this age group, and further evaluate the process and short- and long-term effects of such interventions” (An Y et al, 2009).

#### **Background**

The prevalence of overweight and obesity is increasing in both adult and child populations throughout the world (WHO 2006). Obesity is seen as one of the most important public health threats because of the significant impact of chronic conditions associated with obesity. Obesity in adults increases the risk of cardiovascular diseases, diabetes, and musculoskeletal disorders (Must et al 1999). Obesity is not as strongly associated with morbidity in adolescence <http://archpedi.ama-assn.org/cgi/content/full/158/1/27> - REF-POA20221-4#REF-POA20221-4, but is a strong precursor of obesity and related morbidity in adulthood, with 50% to 80% of obese teenagers becoming obese as adults (Berensson et al 1998, Singh et al 2008). During adolescence, overweight and obesity are often a burden that results in psychosocial problems, poor quality of life and a reduced capacity for physical activity (Hill & Lissau 2002, Molnar & Livingstone 2000, Ravens-Sieberer et al 2001, Fallon et al 2005, Stern et al 2006, de Beer et al 2007). Adolescence is a critical period for the onset of obesity and for obesity-associated morbidity in later life. Therefore, it is important to increase our knowledge and develop effective interventions to prevent and treat over-weight and obesity in adolescence.

*Preventing and treating overweight and obesity.* Overweight and obesity arise from an imbalance between energy intake and expenditure. By adolescence the problem is particularly intractable if overeating is coupled with a lack of physical activity (Whitaker et al 1997). Cochrane reviews have looked upon the effects of treatment and prevention of overweight and obesity in childhood and adolescence (Summerbell et al 2003+2005+2009, Oud Luttikuis 2009). They conclude that so far we lack good quality studies and it is not possible to draw sound conclusions on the most effective interventions related to childhood obesity. However, a comprehensive strategy that addresses dietary and physical activity change, together with psychosocial support and a family focus is recommended (Summerbell et al 2005, Artebaum 2006), and the need for further research is obvious. Adolescents are more concerned about the psychosocial than the physical consequences of their overweight (Booth et al 2008). The psychosocial consequences being ie bullying, social exclusion, inability to participate in mutual activities with peers, leading to low self-esteem and low quality of life (Booth et al 2008, French et al 1996, de Beer et al 2007).

*Interventions aimed at enhancing physical activity.*

Bodyweight is regulated through the interaction of genetic propensity and habitual lifestyle. Genes gives individual disposals for obesity, environment and habitual lifestyle determine if they actually become obese (McArdle et al 2001). According to research findings, the energy intake in Norway has remained stable over the last decades (SEF 2000). It is likely that an increase in body weight can be explained by decreasing daily physical activity due to structural changes in society (Hill & Peters 1998). It is shown that physical activity diminishes from early childhood into adolescence (Sallis et al 1992, Stone et al 1998). Several investigations also point to a lower level of habitual physical activity among persons with overweight problems compared to normal-weighted persons (McArdle et al 2000; Stone et al 1998). Efforts to decrease sedentary activity in youth will affect the incidence of obesity and future physical activity and will reduce future health risks (Douthitt 1994, Kien & Chiodo 2003, Rising et al 1994). Blair et al (1999) have shown that the advantages of being fit are striking and that people can be fit even if they are overweight or obese, and thus they have lowered risk of disease. Therefore, interventions should emphasize increased habitual physical activity more than individual body weight. Unfortunately, the currant emphasis on competitive community sports can act as negative enforcement for increased physical activity by some adolescents, especially those who are clumsy or overweight (Epstein et al 1991, Sallis et al 1992). Therefore, consideration should be given not only to the environments of communities that can promote satisfying physical activity but also to our overall societal outlook toward activity for all individuals, not just for the persons with exceptional athletic competence. In the general population of adolescents, sedentary activity could be replaced by a great variety of physical activities that could increase daily energy expenditure. An important step in behaviour change may be to substitute some physical activity for periods of the day when there is none. This can be activities chosen for pleasure or purpose, but in our view, an individual intervention program should focuses on providing fun physical activity that even unskilled, inactive adolescences can enjoy. It is shown that overweight adolescents endorse extrinsic weight related goals for physical activity, whereas intrinsic goals positively predicts self-determined motivation, quality of life and exercise behaviour (Gillison et al 2006). Motivation is a key factor in the development of successful interventions. Thus, it is important to develop an intervention to enhance physical activity that is perceived as meaningful for the adolescents.

*New means of communication,* such as blogs and chatting on the internet have become widely available and provide excellent opportunities for low threshold counseling using feedback to guide and support over-weight and obese adolescents. Adolescents are familiar with and use the internet frequently to communicate with others. Recent research suggests that internet technology is a promising way to change adolescents' health behavior (An Y et al 2009).

*Quality of life.* Over the last decade, quality of life has emerged as an important concept in evaluating health care with respect to prevention, treatment, and rehabilitation. The concept is based on several key ideas. One idea is that quality of life is a subjective phenomenon in that all individuals have their own perspective concerning their well-being and their lives. Moreover, when used in a medical

context (health-related quality of life, HR-QOL), quality of life is generally conceptualized as a multidimensional construct encompassing domains such as physiological, mental, social, and spiritual areas of life (Eiser et al 2001, Pal 1996, Spilker 1990). HR-QOL measures often consist of multiple items grouped together into various domains of health and functioning. This multidimensionality provides researchers and clinicians with information about the impact of disease, or the effect of various interventions on different aspects of quality of life, and serves as a framework for identifying and developing strategies to promote quality of life (Conolly and Johnson 1999). As overweight and obesity affects both physical and psychosocial areas of life an intervention aimed at promoting health related quality of life seems appropriate. In a qualitative study adolescents say that quality of life is about the positive cycles of life ([name] and Misvær 2010). Feeling good, being satisfied with oneself and having an overall positive attitude are in most cases described as the starting points of a positive cycle. In order to get into and stay in the positive cycle, a positive self-image, good friends and good family relations are important. Consequently, adolescents' quality of life is threatened when these factors are negative. Friends seem to be the most significant factor. Self-image and popularity are factors associated with the ability to get friends ([name] and Misvær 2010).

### **Aim and hypothesis**

The overall purpose of the study is to examine the extent to which a web-based intervention influences physical activity, fitness and quality of life in over-weight and obese adolescents. Further, the aim of this study is to explore and describe how adolescents experience being over-weight and obese, what they perceive as meaningful physical activity and finally how adolescents experience lifestyle changes as demanded in the intervention study.

### **Prevalence and sample characteristics**

For adults, BMI (Body Mass Index; weight in kilograms divided by the square of height in meters) values at or above 25 indicate overweight and a BMI at or above 30 defines obesity. No such generally accepted definitions exist for children and adolescents. However, international standardized cut points have been proposed, among others by Cole et al (2000) and experts support the use of BMI cutoff points for children. The cut points proposed by Cole et al (2000) are widely used and take age, gender and sex into consideration in the estimation. An example of cutoffs for overweight (BMI 25 in adults) and obesity (BMI 30 in adults) in 13 year old adolescents are shown in the table below (Cole, from Nowicka & Flodmark 2006):

| Age | BMI (25)
Boys
Over-weight | BMI (25)
Girls
Over-weight | BMI (30)
Boys
Obese | BMI (30)
Girls
Obese |
|-----|---------------------------------|----------------------------------|---------------------------|----------------------------|
| 13  | 21,91                           | 22,58                            | 26,84                     | 27,76                      |

The prevalence of overweight and obesity of 8 and 12 year old children in Oslo, using Cole's index and based on objective measures of weight and height, was 21 % (Vilimas et al 2005). In another study in Oslo, based on self-reported measures of weight and height, the prevalence was 12% among 15 year old boys and 7 % among 15 year old girls (Lien et al 2007), which is in accordance with the prevalence of self-reported data in several other European countries (Lissau et al 2004). It is shown that the prevalence of overweight might be underestimated by as much as 50% when based on self-reported data (Raben et al 2000). Thus, it is important to get more objective data on weight and height in order to see the true prevalence of the condition and design studies on overweight and obesity using objective measures.

### **Target group**

The present study focuses on adolescents in 7th grade living in Oslo. Since overweight is over-represented in parts of Oslo where the majority of the inhabitants are non-western, it is important to include adolescents with different cultural background and a variation in socioeconomic conditions (Vilimas et al 2005, Lien et al 2007). The target group is overweight adolescents, meaning their BMI is over or equal to the 95th percentile (BMI>25) and they should not have severe health problems as a

result of their overweight. The focus is primarily to prevent a negative development, and the aim is that the school health service in the future might implement a modified version of this strategy for working with overweight adolescents. In another study in Oslo, “Big and strong”, the target group is obese children and the focus is on treating obesity and the program is situated in a hospital (Ullevål University Hospital 2008). Yet another study in Oslo is the “HEIA”-project (<http://www.heia-prosjektet.org/index.html>) which is an intervention study aimed at preventing overweight and obesity among Norwegian children. Young, fit and happy is a study where the target group is in the school health care, the adolescents have a weight problem, but are not being treated medically, and so far very few interventions exist where the intention is to intervene through the ordinary school health service.

### **Design, sample and an overview of the study**

The design of the study is a complex intervention study with a multi-method design, consisting of a randomized controlled trial and a qualitative study. The sample will be drawn from schools in Oslo. Oslo will be divided into four sectors to secure variation on socio-demographic variables. Overweight adolescents will be randomly selected within each sector and placed in the intervention group or control group respectively. The sampling will be based on objective measures of weight and height and using Cole’s index to define overweight and obesity. Weight and height will be measured by the school nurse and will be coordinated with her regular meetings with the adolescents in 7th grade. New guidelines for weight control will be implemented in Norwegian schools, most likely during 2010. This means all pupils in the 7th grade will have their weight and height measured by the school nurse. The study group will receive the web-based intervention and the control group will receive standard care. At baseline, 6 months and 1 year both the experimental group and the control group will be measured at relevant variables. In the qualitative part of the study, in depth interviews with the adolescents in the intervention group will be performed and they will write daily unstructured blogs on the web. The sampling procedure for the qualitative part of the study will follow the sampling procedure of the intervention study. From the intervention group, a strategic or purposive sample of adolescents will be asked to participate in the qualitative part (Gerrish and Lacey 2006). A sample of maximum variation according to gender and socio-demographic variables is intended. Sampling continues until saturation is reached and the adolescents will be interviewed in depth before the intervention starts, further at 6 and 12 months after the intervention is ended.

#### *The study.*

The intervention will consist of three meetings between the adolescent, the parents and the researchers, and weekly web-based blog-counselling. The intervention period is six months and during the intervention and the follow up period the adolescents will be interviewed three times.

Three Meetings. At the 1st meeting the adolescents will fill in the baseline data and the adolescents that consent to take part in the qualitative study will participate in the first interview. The first meeting will also be an introductory meeting where the adolescent and his/her parents will be informed thoroughly about the purpose of the study as a whole and especially about the intervention. It will be made clear that the goal of the intervention is to increase physical activity, fitness and quality of life through meaningful activities. Weight reduction is not focused; however, it is desired to prevent weight gain through increased physical activity. The 2nd meeting will take place one week later and at this meeting the individual intervention is constructed together with the adolescent and the parents. An activity plan is made up according to the following criteria: The goal of the activities is to increase fitness and the activities should be perceived meaningful by the adolescents. Further the activity plan should be made up according to frequency of the activity (preferred daily); intensity of the activity (increased pulse, increased breath frequency); duration of the activity (1 hour a day); variation between purposeful activity (e.g. walking to school) and joyful activities (e.g. joining a dance class), and finally including some social activity. The second meeting should also prepare for the blog-counselling. The 3rd meeting will take place at the end of the intervention (after 6 months) and the purpose is to evaluate the intervention and motivate the adolescent to continue with physical activity. In addition the adolescent will fill in the questionnaires at this time and those participating in the qualitative study will be interviewed. The same instruments will be filled in at a follow-up after 1 year and the third qualitative

interview with the adolescents will take place. In addition qualitative interviews will be performed with the parents of the adolescents taking part in the qualitative study at the one year follow-up.

Diaries and blog-counseling. A web-based, partly structured diary (blog), on activity and narratives about how their day has been is filled in by the adolescents daily. Personal blog-counseling is given once a week during the first three months, thereafter once a month during the next three months. The counselling will be given within in a frame of self-determination theory, the theory of self-efficacy and quality of life. The purpose of this counselling is to give individualised response to each adolescent and support and motivate them according to their needs.

| Overview of the intervention:                                                                                                                                                                                                                                                                                                                                                                                                                                                                                                                                                                                                                                                                                                                                                                                                                                                      | Overview of the qualitative part:                                                                                                                                                                                                                                                                                                                                                                                                                                                                                                                                                                  |
|------------------------------------------------------------------------------------------------------------------------------------------------------------------------------------------------------------------------------------------------------------------------------------------------------------------------------------------------------------------------------------------------------------------------------------------------------------------------------------------------------------------------------------------------------------------------------------------------------------------------------------------------------------------------------------------------------------------------------------------------------------------------------------------------------------------------------------------------------------------------------------|----------------------------------------------------------------------------------------------------------------------------------------------------------------------------------------------------------------------------------------------------------------------------------------------------------------------------------------------------------------------------------------------------------------------------------------------------------------------------------------------------------------------------------------------------------------------------------------------------|
| 
Meeting the adolescent and the parents 1:
 
 
• Base-line (T0)
 
• Introduction
 
 
Meeting the adolescent and the parents 2:
 
 
• Constructing an activity plan
 
• Introducing the blogs and the chat-room
 
• “Starting up”
 
 
Activity plan is carried out
 
 
• Blog-counselling and motivation for six months
 
 
Meeting the adolescent and the parents 3:
 
 
• Evaluating
 
• Filling in questionnaires (T1)
 
• In depth interview 2
 
 
Follow up after one year:
 
 
• Filling in questionnaires (T2)
 
• In depth interview 3
 
 | 
Meeting the adolescents 1:
 
 
• Qualitative in-depth interviews with adolescents (T0)
 
 
During the intervention period:
 
 
• Unstructured blog narratives
 
 
Meeting the adolescents 3:
 
 
• Qualitative in-depth interviews with adolescents (T1)
 
 
Follow up after one year:
 
 
• Qualitative in-depth interviews with adolescents and parents (T2)
 
 |

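### The arm appears to be known at or around baseline, and the intervention arm's six-month questionnaires are tied to a motivational meeting, so entry and self-reports can depend on arm

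*Protocol*

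**What the plan says.** All references are to the Protocol.

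- **Selection and allocation** (Design, sample and an overview of the study): "Overweight adolescents will be randomly selected within each sector and placed in the intervention group or control group respectively". The basis is the school nurse's measurements of weight and height. No later point of randomisation is given.
- **What the intervention is** (The study): "The intervention will consist of three meetings between the adolescent, the parents and the researchers, and weekly web-based blog-counselling". The overview table also lists the baseline measurement and the introduction under the intervention, at meeting 1.
- **Meeting 1** (The study): T0 is filled in there, and the first in-depth interview is held there with "the adolescents will fill in the baseline data and the adolescents that consent to take part in the qualitative study". It is also the occasion "where the adolescent and his/her parents will be informed thoroughly about the purpose of the study as a whole and especially about the intervention". Families are told that "the goal of the intervention is to increase physical activity, fitness and quality of life through meaningful activities".
- **Who is interviewed** (Design, sample and an overview of the study): "From the intervention group, a strategic or purposive sample of adolescents will be asked to participate in the qualitative part".
- **Meeting 3** (The study): at six months "the purpose is to evaluate the intervention and motivate the adolescent to continue with physical activity". The questionnaires are completed on the same occasion.
- **Controls** (Design; Data collection and measures): they are measured at baseline, 6 months and 1 year and complete the same instruments. Where, by whom and after what introduction is not described.
- **Consent** (Research ethics): required from adolescents and parents, with no timing relative to allocation.

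**The concern.** Two things are at stake.

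The first is comparability at entry and at baseline. If families can learn the arm before they agree to take part, those who enter the two arms may differ in ways that randomisation was meant to prevent. If T0 questionnaires are answered with the arm known, T0 is no longer a clean baseline.

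The second is measurement at T1. Physical activity, quality of life, self-efficacy and exercise motivation are self-reported. An adolescent who answers on an occasion devoted to reviewing the programme and encouraging further activity may answer more favourably than one who answers elsewhere. Families have also been told at meeting 1 that activity and quality of life are what the programme should improve.

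Both are matters of trial conduct, to be settled before enrolment. A larger sample removes neither.

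**Working it through.** **Step 1. Order of events at entry.**

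1. The Design section describes selection and placement in arms as one act, following the school nurse's measurements.
2. Meeting 1 comes later. It is counted among the intervention's meetings and contains both T0 and the introduction.
3. The first interview is also at meeting 1, and interviewees come only from the intervention group.
4. An interview restricted to one arm cannot be held unless the arm is known by then.

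Points 1 to 4 make it most natural to place allocation at or before meeting 1. The order of forms, introduction and interview within the meeting is not fixed, and consent is not timed. Nothing in the text therefore prevents entry or T0 answers from depending on arm.

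**Step 2. Setting at T1.** For the intervention arm the text is explicit: the questionnaires belong to the same occasion as the evaluation and motivation. For controls no setting is given. The protocol does not require the two to match.

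**Step 3. The plan's own sample size.** Inputs from the Sample section: effect size 0.5, two-sided alpha 0.01, power 0.80.

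- Normal approximation: n = 2 × (2.576 + 0.842)² / 0.5² = 93.4, so 94 per arm.
- Two-sample t test: 95.1, so 96 per arm, which matches the stated 96. The protocol then plans 100 + 100.

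The figure is not in dispute. It supplies the 100 per arm and the alpha used next.

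**Step 4. Illustrative size of an entry bias.** The documents give no inputs, so these are assumptions: refusal differs between arms by 10 to 20 percentage points, and decliners differ from acceptors by 0.25 to 0.5 SD.

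- Bias = difference in refusal × difference between decliners and acceptors.
- Low end: 0.10 × 0.25 = 0.025 SD. High end: 0.20 × 0.5 = 0.10 SD.
- As a share of the planned 0.5 SD: 5% to 20%.

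For an unadjusted two-sided z test with 100 per arm, the standard error is √(2/100) = 0.1414 SD. The true type I error is P(|Z + shift| > critical value), with shift = bias / 0.1414.

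| Assumed bias (SD) | Shift | Alpha 0.01 | Alpha 0.05 |
|---|---|---|---|
| 0 | 0 | 0.010 | 0.050 |
| 0.025 | 0.177 | 0.011 | 0.054 |
| 0.10 | 0.707 | 0.031 | 0.109 |

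**Step 5. Allowing for the planned model.** The Analysis section plans repeated-measures mixed models.

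- In a group-by-time contrast, a level difference that is the same at T0 and T1 cancels.
- With baseline adjustment and an assumed T0–T1 correlation of 0.6, a stable 0.10 SD leaves 0.10 × (1 − 0.6) = 0.04 SD. The standard error becomes 0.1414 × √(1 − 0.36) = 0.1131 SD, and the shift is 0.04 / 0.1131 = 0.354. The type I error is then about 0.015 at alpha 0.01 and 0.064 at alpha 0.05.

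This relief assumes a stable difference and an undistorted T0. It does not apply to a shift that arises only at T1, and a T0 distorted by knowledge of the arm passes into the estimated change.

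**The case against.** The strongest reply is that much of this is read from an unclear text.

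- **Consent may come first.** The requirement for informed consent carries no timing, and the only consent mentioned under The study concerns the qualitative part. A reader might infer that families are first informed at meeting 1 and accept or decline knowing their arm. The text does not say so. This stands: arm-dependent entry is a risk left open, not a demonstrated fact.
- **T0 may precede disclosure.** The interview shows that the arm is known by the time of the interview, not when the forms are filled in. The Design section places the interview before the intervention starts, Data collection describes T0 as preceding the intervention, and the overview table puts the start-up at meeting 2. This also stands, and rules out saying that the arm must be known when T0 is completed. It does not supply the missing requirement that T0 be finished before allocation is revealed.
- **The control setting is undescribed, not shown to differ.** Correct. Nor does the text say that parents or researchers are present while the forms are completed, or that the forms follow the talk. What remains is that one arm's T1 forms are explicitly tied to the motivational meeting and no common setting is required.
- **Fitness.** A reader might extend the concern to the shuttle run, which depends on effort. The documents do not support that: meeting 3 is named for the questionnaires, and no section says where the run is done.
- **Size.** The bias inputs are assumed, the low end leaves the error rate almost nominal, and the unadjusted test is not the planned analysis. All of this stands.

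**Conclusion.** The concern holds in a limited form. The protocol does not require consent and T0 before allocation, and its description most naturally places knowledge of the arm at or around T0. It explicitly has the intervention arm complete the T1 questionnaires on an occasion meant to evaluate and motivate, without a matching setting for controls. Entry, T0 self-reports and T1 self-reports can therefore depend on arm.

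The size is unknown. Under assumed biases of 0.025 to 0.10 SD, the unadjusted comparison at alpha 0.01 has a true type I error of about 0.011 to 0.031. The repeated-measures model would reduce or remove the part due to a stable baseline difference, but not a shift specific to T1. The direction of any selection bias cannot be told from the text; a reporting shift at meeting 3 would more plausibly favour the intervention.

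**What to change.** State the order in the protocol:

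1. Obtain consent and complete T0, in the same format, for all eligible adolescents.
2. Then reveal a concealed 1:1 allocation within each sector.
3. Hold the first in-depth interview with the intervention-arm subsample after allocation, in the one-week gap that already exists before meeting 2.
4. At T1 and T2 have both arms complete the questionnaires in the same format. In the intervention arm this comes before any evaluation, motivational talk or interview.

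The cost is a small scheduling change. The first interview moves by a few days at most. Control sessions have to be matched in format, but controls are already measured at all three time points. The sample size does not change.

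Participants cannot be blinded to a counselling programme, so some reporting bias will remain even in a common setting. The protocol should acknowledge this as a limitation of the self-reported outcomes.
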